#### Primary outcomes

2.9.1

The primary outcome was changes in asthma symptom control, measured using the Childhood Asthma Control Test (C-ACT) at baseline, discharge, and post-intervention. Given the nested longitudinal structure of repeated measurements within families, we employed multilevel negative binomial models to analyze asthma symptom frequency (count data), estimating incidence rate ratios (IRRs) and 95% confidence intervals (CIs).

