### Questionnaires

2.11

Childhood Asthma Control Test (C-ACT): The C-ACT is an important tool for measuring how well asthma symptoms are controlled in children. It has two parts with a total of seven questions in Chinese version. The first part has four questions for the child to answer. Each question is scored from 0 to 3, based on how the child feels about their asthma control. The second part has three questions for the parent to answer. Each question is scored from 0 to 5, based on how often the child has asthma symptoms in the last four weeks. The total score of the C-ACT goes from 0 to 27. A score of 23 or higher means asthma is fully controlled, with few symptoms affecting daily life. A score between 20 and 22 means partial control, where symptoms are somewhat managed, but some problems remain. A score of 19 or less means asthma is not controlled, and stronger treatments may be needed (31).Short-Form Egna Minnen av Barndoms Uppfostran for Chinese (s-EMBU-C): The s-EMBU-C is a questionnaire designed to evaluate how children see their parents’ parenting styles. The child fills out this questionnaire. There are separate versions for fathers and mothers. Each version has 21 questions, divided into three parts: rejection (6 items), emotional warmth (7 items), and overprotection (8 items). The questions are scored using a scale from 1 to 4. “Never” gets 1 point, “Occasionally” gets 2 points, “Frequently” gets 3 points, and “Always” gets 4 points. Item 15 is scored in reverse. The scores for each part are found by adding up the points for each question in that part. A higher score in a part means the parent shows that parenting style more often. The total score for both versions can range from 28 to 112 points (32).The assessment of depression and anxiety will use the Chinese version of the Patient Health Questionnaire-4 (PHQ-4). This is a short self-report tool to check depression and anxiety symptoms over the past two weeks. The PHQ-4 has four questions. The first two questions focus on depression symptoms, and the last two focus on anxiety symptoms. Each question is rated on a scale from 0 to 3: “Not at all” (0 points), “Several days” (1 point), “More than half the days” (2 points), and “Nearly every day” (3 points). The total score goes from 0 to 12. In studies in China, the PHQ-4 has shown high validity and reliability, with a Cronbach’s alpha of 0.833 (33).The Chinese version of the Perceived Social Support Scale-Short Form (PSSS-SF) is used to measure the level of social support a person feels they receive. The scale has three questions, each about a different type of support: family support (Item 1), friend support (Item 2), and other support (Item 3). Each question is scored on a 7-point scale from 1 (Strongly Disagree) to 7 (Strongly Agree). The total score can range from 3 to 21. Higher scores mean more social support, showing that the person’s social network provides more help, both emotionally and practically (34).The Chinese version of the New General Self-Efficacy Scale (NGSES-SF) is used to measure a person’s confidence in their ability to succeed in tasks or face challenges. It has three questions, each focusing on a different aspect of self-efficacy. Item 1 looks at how capable a person feels in handling a situation. Item 2 focuses on how confident a person is in their skills. Item 3 looks at how confidence in one area can apply to other areas. The NGSES-SF uses a 5-point Likert scale. Respondents can choose from 1 (Strongly Disagree), showing low confidence, to 5 (Strongly Agree), showing high confidence. The total score can range from 3 to 15 (35).The Chinese version of the EQ-5D-5L scale (EuroQol-5 Dimensions 5 Levels) will be used to measure quality of life. The scale looks at five important health areas: mobility, self-care, usual activities, pain/discomfort, and anxiety/depression. For each area, there are five levels, ranging from “no problems” to “extreme problems.” This lets respondents choose the level that best matches their condition. It gives a complete view of a person’s health in these five areas. The EQ-5D-5L also includes a Visual Analogue Scale (VAS). This part lets participants rate how they feel about their current health on a scale from 0 to 100. A score closer to 0 means worse health, while a score closer to 100 shows better health (36).Smoking behavior will be assessed using a self-designed questionnaire. The questionnaire has four multiple-choice questions to categorize smoking habits. These questions are meant to find out: whether the person smokes, how long it has been since they quit smoking (if they quit), how many cigarettes they smoke daily, and when they started smoking. The first question is “Do you have a smoking habit?” with these options: (1) Yes, I smoke regular cigarettes; (2) Yes, I smoke e-cigarettes; (3) I smoke both; (4) I used to smoke (now quit); (5) I have never smoked. Based on their answers, participants will be grouped into two categories: smokers, which include people who currently smoke regular cigarettes, e-cigarettes, or both; and non-smokers, which include those who have never smoked and those who have quit smoking (37).Alcohol consumption will be evaluated using a self-developed 7-item multiple-choice questionnaire designed to assess: 1) current/historical alcohol use status, 2) age of drinking initiation, 3) age of drinking cessation (if applicable), 4) preferred alcoholic beverage types, 5) average daily alcohol intake, 6) pre-quitting daily consumption volume, and 7) perceived anxiety related to alcohol cessation. The instrument begins with the core screening question: ‘Which best describes your alcohol consumption pattern?’ Respondents choose from four mutually exclusive categories: (1) Never consumed alcohol; (2) Current regular drinker; (3) Former drinker who has quit; (4) New-onset drinker in the past year (43, 44).The Chinese version of the Pittsburgh Sleep Quality Index Short Form (PSQI-SF) is a shorter version of the Pittsburgh Sleep Quality Index, made to measure sleep quality. The scale has six items, covering five key aspects of sleep. Items 1 and 2 measure sleep efficiency. Item 3 measures how long it takes to fall asleep. Item 4 looks at sleep duration. Item 5 checks for sleep disturbances. Item 6 looks at overall sleep quality. The total score on the PSQI-SF goes from 0 to 15. A higher score means worse sleep quality (38).The Chinese version of the Family Communication Scale Short Form (FCS-SF) is made to measure how well family members communicate. The scale has four items that assess family communication. It uses a 5-point Likert scale, where 1 means “strongly disagree” and 5 means “strongly agree.” The total score goes from 4 to 20. A higher score means better communication among family members (39).The Chinese version of the Electronic Health Literacy Scale (eHEALS) measures how well parents of children can search for, evaluate, and use electronic health information to solve health problems. The scale has five items in one dimension. It uses a 5-point Likert scale, where 1 means “strongly disagree” and 5 means “strongly agree.” The total score ranges from 5 to 25. A higher score means better electronic health literacy (40).

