
### Statistical analysis

2.12

This study will collect quantitative data through questionnaires and process the data using Microsoft Excel. Data analysis will follow the intention-to-treat principle. For continuous variables, descriptive statistics will show means ± standard deviations or medians and interquartile ranges (P25, P75), depending on the data. Normally distributed continuous variables will be compared using the Student’s t-test or one-way analysis of variance (ANOVA). Non-normally distributed data will be analyzed with non-parametric tests. The normality of the data will be checked using the Kolmogorov-Smirnov test. Categorical variables will be shown as sample percentages (n) and analyzed using the Chi-square test. For missing data, multiple imputation using chained equations (MICE) will be used, with 50 iterations to ensure convergence. The imputation method will be predictive mean matching (PMM), with 5 neighbors and 20 imputed datasets.

In the cross-sectional data analysis, this study will use linear regression, logistic regression, and structural equation modeling (SEM) to examine the relationships between behavioral patterns and mobile health applications. Given the nested structure of parent-child dyads within families, we employed multilevel models with family-level random intercepts to account for within-family correlations. For child health outcomes (asthma-related events and symptoms), a two-level negative binomial model was utilized to estimate IRRs and 95% CIs, adjusting for family-level variables (parents’ parenting styles, household income, marital status) and child-level variables (age, sex). For parental outcomes (continuous data), a two-level linear mixed model was applied to evaluate intervention effects, adjusting for family-level variables (marital status, household income) and parent-level variables (age, education, parents’ parenting styles). *Post hoc* comparisons of estimated marginal means were conducted using the emmeans package to test between-group differences. Model fit was validated through convergence checks, residual analysis, and overdispersion testing for count data. All analyses were performed in R (version 4.3.1; R Foundation for Statistical Computing, Vienna, Austria) using the lme4 package (version 1.1-33). An independent statistician with no conflicts of interest conducted the analysis. All statistical tests were two-tailed, with a significance level of 0.05.

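### The primary outcome is the C-ACT score, but the only model stated beside it is a negative binomial for symptom counts, so the C-ACT has no fitting longitudinal or adjusted model

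*Protocol article*

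**What the plan says.** Section 2.9.1 (Primary outcomes) has two sentences. The first defines the endpoint: "The primary outcome was changes in asthma symptom control, measured using the Childhood Asthma Control Test (C-ACT) at baseline, discharge, and post-intervention". The second gives the model, justified by repeated measurements within families: "we employed multilevel negative binomial models to analyze asthma symptom frequency (count data), estimating incidence rate ratios (IRRs") with 95% confidence intervals.

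Section 2.11 (Questionnaires) defines the score. On the child part: "The first part has four questions for the child to answer. Each question is scored from 0 to 3". On the parent part: "The second part has three questions for the parent to answer. Each question is scored from 0 to 5". On range and direction: "The total score of the C-ACT goes from 0 to 27. A score of 23 or higher means asthma is fully controlled".

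Section 2.12 (Statistical analysis) divides the models by type of outcome. For children: "For child health outcomes (asthma-related events and symptoms), a two-level negative binomial model was utilized to estimate IRRs and 95% CIs". For parents: "For parental outcomes (continuous data), a two-level linear mixed model was applied to evaluate intervention effects". It also has a general sentence comparing continuous variables by t-test or ANOVA, or by non-parametric tests if not normal. The dispersion check it names is for overdispersion.

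Symptom days, night awakenings, activity-limited days and reliever days are listed in section 2.9.2, as secondary outcomes.

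**The concern.** The stated endpoint and the stated model do not belong together. The endpoint is a bounded sum of seven ordinal items on which a higher value is good. The model is for unbounded event counts, and its effect measure is a ratio of rates. Three things are at stake:

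- **Which variable is primary.** A reader cannot tell whether the primary result will be a C-ACT comparison or a ratio of symptom counts.
- **How the result reads.** If the C-ACT is the modelled variable, a ratio above 1 is a benefit, yet it carries the label of a symptom incidence rate. A ratio also sits badly with a capped score whose control categories are set in points.
- **Precision.** A negative binomial cannot represent a variance smaller than its mean. A capped score can easily have one, and the standard error is then overstated.

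**Working it through.** **1. The plan's own figure.** Four items at 0 to 3 and three at 0 to 5 give a maximum of 4 × 3 + 3 × 5 = 27. The stated range of 0 to 27 reproduces. The score is bounded and higher is better.

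**2. Which variable does the count model serve?** The text does not name the C-ACT as its dependent variable. Three features point that way: the sentence stands under the primary-outcome heading; its reason is repeated measurement, and the three C-ACT visits have just been listed; and Table 1 schedules the C-ACT at all three visits but has no row for symptom-day counts. The other reading is that the sentence belongs to the counts in section 2.9.2 and is misplaced. Then the C-ACT has no longitudinal or adjusted model. The text needs correction on either reading.

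**3. Direction and scale, if the C-ACT is modelled.** With assumed means of 22 (intervention) and 20 (control), IRR = 22 / 20 = 1.10, which is a benefit. The same ratio applied to an expected score of 25 gives 25 × 1.10 = 27.5, above the maximum.

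**4. Variance floor.** Negative binomial variance is μ + αμ² with α ≥ 0, so the model SD cannot fall below √μ: 4.24 at mean 18, 4.47 at 20, 4.69 at 22, 4.90 at 24.

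**5. Effect on the standard error, one time point.** The documents give no C-ACT mean, SD or within-child correlation, so these are assumptions. For SD below √μ, the ratio of model SE to true SE is √μ / SD. At mean 20 and SD 3 this is 4.47 / 3 = 1.49. A simulation checked it: 25 per arm (the target in section 2.4), rounded scaled-beta scores on 0 to 27, negative binomial by maximum likelihood against a t-test, 2,000 runs per setting. Type I error is at 20 vs 20, power at 20 vs 22.

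| SD | SE ratio, formula | SE ratio, simulated | Type I error, NB / t | Power, NB / t |
|---|---|---|---|---|
| 2.5 | 1.79 | 1.75–1.80 | 0.001 / 0.052 | 0.23 / 0.78 |
| 3 | 1.49 | 1.51–1.52 | 0.003 / 0.046 | 0.27 / 0.63 |
| 3.5 | 1.28 | 1.26–1.28 | 0.007 / 0.061 | 0.28 / 0.49 |
| 4 | 1.12 | 1.11–1.15 | 0.032 / 0.050 | 0.33 / 0.42 |
| 4.5 | – | 1.05 | 0.038 / 0.041 | 0.32 / 0.35 |
| 5 | – | 1.00–1.02 | 0.056 / 0.051 | 0.30 / 0.30 |
| 6 | – | 1.04–1.05 | 0.043 / 0.046 | 0.21 / 0.22 |

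**6. With the planned random intercept.** For a change over time, the within-child SD is what the count part must fit. The ratio is then about √μ / (SD × √(1 − ICC)). At mean 20 and an assumed ICC of 0.5 it is 2.1 at total SD 3, 1.6 at SD 4, 1.26 at SD 5 and 1.05 at SD 6. This step is by formula only and was not simulated.

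**The case against.** The best defence is that the protocol never says the C-ACT enters the negative binomial. The model is attached to symptom frequency in section 2.9.1 and to events and symptoms in section 2.12, and section 2.9.2 lists counts that match. For those counts the model type is reasonable and an IRR below 1 correctly means benefit. This stands as a possible reading, but it does not clear the plan, because the C-ACT is then left without an adjusted model.

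A reader might infer that the primary outcome cannot be validly analysed at all. The documents do not support that. The general t-test, ANOVA or non-parametric route in section 2.12 is open to the C-ACT and is valid under randomisation. It uses neither the baseline score nor the repeated measurements.

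The trial is also a pilot, and section 2.4 disclaims hypothesis testing, so lost power weighs less than in a confirmatory trial. But section 2.12 sets two-sided tests at 0.05, and the abstract and discussion make improved symptom control the main aim. Section 2.4 also wants outcome variability for later use, and an IRR does not give that in C-ACT points.

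Leaving detail to an analysis plan is no answer here: a model is stated under the primary outcome, and it does not fit.

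**Conclusion.** The point holds: as written, the stated analysis does not fit the stated primary outcome, and section 2.12 does not repair it. This rests on the text alone.

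The consequences are conditional on the C-ACT being the modelled variable. A reader might infer that the IRR would be reversed. It would not be: the estimate is sound as a ratio of mean scores, and only its label misleads. A reader might also infer that the intervals are certain to be wrong or that false positives are inflated. Neither follows. At one time point and mean 20, the standard error is about 1.5 times too large at SD 3 and 1.1 times at SD 4, and the problem is essentially gone by SD 4.5 to 5. With a random intercept it can persist at a larger total SD, because only the within-child part counts. Where the standard error is wrong it is too large: the test is conservative and the loss is in power and precision. The planned overdispersion test is not aimed at this, although the residual analysis might show it. The mean, SD and ICC are all assumptions.

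**What to change.** In sections 2.9.1 and 2.12:

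- Name the C-ACT total as the primary dependent variable.
- Analyse it with a baseline-adjusted linear model: either ANCOVA at 3 months, or a linear mixed model with group-by-visit terms and adjustment for baseline C-ACT.
- Report the difference in mean C-ACT points with its 95% confidence interval.
- Keep the negative binomial and IRRs for the true counts in section 2.9.2 (symptom days, night awakenings, activity-limited days, reliever days), and move the count-model sentence there.

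The cost is a few sentences of text. The lme4 package already named fits the mixed model, and no new data, visits or participants are needed.

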#### Secondary outcomes

2.9.2

Physiological Control of Children: The assessment indicators cover multiple aspects. In terms of pulmonary function, key parameters such as pulmonary ventilation function and expiratory flow rate will be detected by professional equipment; the average number of days with asthma symptoms, record the number of days when children experience asthma-related symptoms within a certain period; the number of nights awakened due to asthma symptoms; the number of days with activity limitations due to asthma; the number of days per week requiring inhaled bronchodilators for symptom relief; height, weight, waist circumference, body mass index (BMI); the 30 - day readmission rate; the length of hospital stay.Parental Behavior Changes: Parental behavioral changes will be measured using specific instruments, including a self-developed questionnaire to assess frequency and exposure to smoking and alcohol consumption; the Pittsburgh Sleep Quality Index Short Form (PSQI-SF) to evaluate sleep patterns; and the EQ-5D-5L (EuroQol-5 Dimensions 5 Levels) scale for measuring overall quality of life.Parental Social Cognition and Psychology: Self-efficacy; depression, anxiety, stress levels; social support.

In addition, the recruitment rate, dropout rate, and reasons for withdrawal will be collected. During the data analysis phase, in order to assess the homogeneity of the data, the demographic characteristics and study outcomes of those who dropped out will be compared to determine whether the dropout situation has an impact on the overall effectiveness of the study.

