### Randomization and blinding

2.2

In this study, the randomization procedure uses a computer-generated sequence of random numbers. Patients will be assigned to the intervention and standard care groups in a 1:1 ratio. This randomization process will take place prior to patient admission. The aim is to ensure that each patient is assigned to the appropriate study group in a predefined order, thus ensuring randomization and fairness of allocation. When patients are admitted to the hospital, they will be assigned a unique code. This code is consistent with the sequence of random numbers and ensures smooth and consecutive enrollment of patients. Once randomization is complete, patients are directed to the appropriate hospital room based on their grouping. Specifically, patients in the intervention group are sent to Ward A, while those in the control group are sent to Ward B to prevent any possible cross-talk between the different interventions.

To ensure the confidentiality of the allocation sequence, an independent team member will be responsible for the randomization process and be neither involved in participant registration nor in intervening in the allocation. This is to prevent disclosure of the sequence during the course of the study. This team member then forward the allocation results to the intervention team. By doing this, both the participant enrollment team and the intervention team know nothing about the allocation in advance.

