### Sample size

2.4

Given that this study is a pilot RCT, its primary focus is on evaluating the feasibility and practical implementation of the AI-HEALS intervention. Therefore, it is not designed to perform statistical hypothesis testing but rather to collect preliminary data on intervention operability and acceptability. As such, the sample size estimation for this pilot RCT does not follow traditional power analysis methods used for hypothesis testing. Instead, a pragmatic rule of thumb was applied to select a sample size sufficient to determine outcome variability and identify any operational issues (27). In line with the suggestions put forward by Billingham et al., the sample size for this pilot study is set at around 25 participants per group, amounting to a total of 50 participants (27). Anticipating an attrition rate of 20%, we determined that a minimum total sample of 60 participants (30 per group) would be necessary.

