Based on this, the study will conduct a pilot randomized controlled trial to assess the effectiveness and acceptability of the AI-HEALS system in controlling asthma in children. The main purpose was to evaluate whether the intervention of C-ACT measurement after the intervention improved the control of asthma symptoms. Secondary outcomes include physical health indicators such as lung function, BMI, and hospitalization rates, as well as behavioral and psychological outcomes related to parental involvement, self-management strategies, and overall child quality of life. These outcomes will be measured using quantitative methods (e.g., standardized questionnaires and physiological assessments) and qualitative interviews. Given the medical and behavioral factors involved in childhood asthma, AI-HEALS has great potential to increase patient engagement and improve adherence to treatment regimens.

Although the interventions proposed in this study show considerable potential, some limitations must be recognized. First, the generalizability of the findings may be limited by inclusion criteria that focus on specific populations and clinical characteristics. For example, this study focused on children with asthma who were willing to use digital health interventions and may not have included those with lower health literacy or those less comfortable using technology. Second, while this study will provide valuable insights into the efficacy of the AI-HEALS system, there may be challenges in interpreting the numerous external factors that influence asthma control. Environmental triggers, socioeconomic status, and access to healthcare are all important variables that may influence outcomes, but it may be difficult to fully control for them in the real world. This study will include demographic and clinical covariates in its analysis in an attempt to account for some of these factors, although residual confounders may still affect outcomes. Finally, although the study aims to ensure data accuracy through rigorous monitoring procedures, issues such as participant dropout or missing data may still affect the validity of the findings. The research team plans to use multiple interpolation techniques to address these challenges, but the potential bias of missing data must still be considered.

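### Comparing dropouts' demographics and study outcomes can describe who left, but cannot determine whether dropout affected the effectiveness result, as the protocol says it will

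*Protocol article*

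**What the plan says.** After listing the secondary outcomes, section 2.9.2 commits to collecting the recruitment rate, the dropout rate and the reasons for withdrawal. It then says that, along with demographic features, "study outcomes of those who dropped out will be compared to determine whether the dropout situation has an impact on the overall effectiveness of the" trial. It does not name the comparison group, the outcome or the time point.

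Other parts of the article bear on this:

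- **Primary outcome (2.9.1):** asthma control, "measured using the Childhood Asthma Control Test (C-ACT) at baseline, discharge, and post-intervention". The Discussion states the main aim as improvement in C-ACT after the intervention.
- **Sample size (2.4):** "Anticipating an attrition rate of 20%, we determined that a minimum total sample of 60 participants (30 per group) would be necessary".
- **Statistical analysis (2.12):** "For missing data, multiple imputation using chained equations (MICE) will be used, with 50 iterations to ensure convergence". Imputation is by predictive mean matching (PMM) with 5 neighbours and 20 datasets.
- **Withdrawal (2.3.3 and 2.6):** participants with qualifying serious adverse events leave the study. Families who withdraw once the intervention has begun count as attrition. The only later contact stated for them is an interview about reasons, where feasible.
- **Discussion (5):** after multiple imputation, "the potential bias of missing data must still be considered".

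**The concern.** The sentence in 2.9.2 fixes both a procedure and the conclusion to be drawn from it. Effectiveness rests on the 3-month C-ACT, which a family that has left will normally lack. What the check can use is either observed data from before the family left or, if someone chose to use them, imputed 3-month values. Neither carries information on how the family fared after leaving, so neither can settle whether dropout changed the effectiveness estimate.

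The risk is that an unremarkable comparison is later reported as evidence that dropout did no harm. The article describes no other analysis aimed at that question. Dropout that differs between arms is plausible, because only AI-HEALS families are asked for weekly uploads and have their engagement reviewed each week (2.7.2 and 2.8).

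**Working it through.** **1. Number of dropouts.** Section 2.4 starts from "around 25 participants per group, amounting to a total of 50 participants". Its total is reproduced as 50 × 1.2 = 60. With 20% attrition, 60 × 0.20 = 12 drop out and 48 complete. Given "Patients will be assigned to the intervention and standard care groups in a 1:1 ratio", that is about 6 and 24 per arm if dropout is equal. (Dividing instead, 50 / 0.8 = 62.5, gives 63; that is a separate matter.)

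**2. What each reading of the comparison can show.**

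| Values compared | Observed in dropouts? | Can show | Cannot show |
|---|---|---|---|
| Baseline C-ACT | Yes | Who left | Course after leaving |
| Discharge C-ACT | Yes, if they left after discharge | Who left, including those already worse | Course after leaving |
| 3-month C-ACT, imputed | No; PMM copies values from participants with similar predictions | What the earlier data predict | Worsening after the last observed visit |

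**3. Precision if true 3-month values were known.** Two-sided alpha is 0.05 (2.12). In SD units the standard error for 12 vs 48 is √(1/12 + 1/48) = 0.323.

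- Gap of 0.5 SD: 0.5 / 0.323 = 1.55, and Φ(1.55 − 1.96) = 0.34. The t-test calculation gives 0.33.
- Gap of 1.0 SD: power is 0.87.
- Within one arm, 6 vs 24: the standard error is √(1/6 + 1/24) = 0.456, and power for 0.5 SD is 0.19.
- The 95% CI half-width for 12 vs 48 is 1.96 × 0.323 = 0.63 SD, so an observed difference of zero is still compatible with a sizeable gap.

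**4. Simulation.** There were 1,500 trials per setting with 30 per arm and 6 dropouts per arm. Baseline and discharge were observed for everyone. The 3-month score was imputed from baseline, discharge and arm by PMM (5 neighbours, 20 datasets). Gaps of 0 to 1.5 SD and correlations of 0.3 and 0.6 between visits are assumptions. The last four columns give the share of runs with p < 0.05. Results for a true gap of 1.0 SD:

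| Scenario | Correlation | Mean imputed gap (SD) | True values | Pooled imputed | Single imputed dataset | Observed discharge |
|---|---|---|---|---|---|---|
| Worse only after discharge | 0.3 | 0.00 | 86% | 0% | 3% | 5% |
| Worse only after discharge | 0.6 | 0.00 | 86% | 0% | 4% | 5% |
| Already worse at baseline and discharge | 0.3 | 0.34 | 86% | 1% | 19% | 87% |
| Already worse at baseline and discharge | 0.6 | 0.59 | 87% | 18% | 48% | 87% |

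In the first scenario the imputed gap stayed at 0.00 for true gaps of 0.5, 1.0 and 1.5 SD and for both correlations. The discharge comparison flagged a difference at about the chance rate. In the second scenario the observed discharge comparison worked well.

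**5. Why arm matters (illustration, all inputs assumed).** Suppose dropouts are g points worse at 3 months than their imputed values, and the dropout proportions are p₁ (AI-HEALS) and p₀ (control). The between-arm mean difference is then off by (p₁ − p₀) × g. With 30% vs 10% and g = 3, this is 0.20 × 3 = 0.6 C-ACT points. For g from 1 to 4 it runs from 0.2 to 0.8. With equal dropout and equal g it is 0.

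**The case against.** The strongest reply is that this is an ordinary attrition check described loosely. Much of that reply stands.

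- A reader might infer that dropouts will have no study outcomes, or only imputed ones. The documents do not support this. Table 1 schedules C-ACT, lung function and several scales at baseline and discharge, and these are real data for anyone leaving after discharge.
- A reader might infer that imputed values will enter the comparison. Section 2.9.2 does not mention imputation and 2.12 does not mention the dropout comparison, so the 0.00 SD result applies only under that reading, and only to worsening after the last observed visit.
- A reader might infer that the check will generally report no impact even when dropouts did clearly worse. The second scenario contradicts this: families already 1.0 SD worse were flagged in 87% of runs on observed discharge scores.
- A reader might infer a rule under which a non-significant test clears the trial, or that arms will not be compared. Section 2.9.2 ties no test or threshold to the check and names no comparator, so it neither includes nor excludes arm. Such detail may stand in the full protocol or analysis plan.
- The Discussion concedes residual bias from missing data, and 2.4 says the pilot is not designed for hypothesis testing.

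The stated purpose of the comparison is not rescued. Whichever comparator and time point are chosen, it does not determine the effect of dropout on the result. If the full protocol continues 3-month assessment of withdrawn families who agree, the problem shrinks to those who are truly lost.

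**Conclusion.** The point holds in a limited form. The comparison is worth doing, but the conclusion attached to it in 2.9.2 does not follow. Observed baseline and discharge data describe who left. They do not show what happened afterwards, and PMM values would not show it either. A null comparison is also weak evidence with about 12 dropouts against 48 completers (power about 33% for 0.5 SD, with true outcomes known).

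This rests on the protocol's own 20% attrition and on no 3-month data being obtained from withdrawn families, which is how the article reads. The effect sizes, correlations and C-ACT shifts are assumptions. The 0.6-point figure is an illustration, not an estimate of bias in this trial. Severity is minor to moderate: the trial is a pilot and the article already admits residual bias, but it also states effectiveness aims and gives this check as the way to judge dropout.

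**What to change.** Replace the sentence in 2.9.2 with the following:

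- **(a)** Report the number of dropouts and their reasons by arm and by time (before or after discharge).
- **(b)** Compare observed baseline and discharge C-ACT of dropouts and completers within arm, before imputation, as differences with 95% CIs. Describe this as characterising who dropped out.
- **(c)** Assess impact by rerunning the planned MICE with imputed 3-month C-ACT shifted over a range, for example 1 to 4 points lower in the AI-HEALS arm (the range is an assumption), and report how far the between-arm estimate moves. For orientation, with 6 of 30 imputed the unadjusted arm mean moves by 0.20 × 1 = 0.2 to 0.20 × 4 = 0.8 points.
- **(d)** Delete the statement that the comparison determines whether dropout had an impact.

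The cost is a few lines of text and a few extra analysis runs. No new data are needed.
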